## Abstract

**Background:**

The electronic health record (EHR) of the general physician (GP) is an important tool that can be used to assess and improve the quality of healthcare. However, there are some problems when (re) using the data gathered in the EHR for quality assessments. One problem is the lack of data completeness in the EHR. Audit and feedback (A&F) is a well-known quality intervention that can improve the quality of healthcare. We hypothesize that an automated A&F intervention can be adapted to improve the data completeness of the EHR of the GP, more specifically, the number of correctly registered diagnoses of type 2 diabetes and chronic kidney disease.

**Methods:**

This study is a pragmatic cluster randomized controlled trial with an intervention at the level of GP practice. The intervention consists of an audit and extended electronically delivered feedback with multiple components that will be delivered 4 times electronically to general practices over 12 months. The data will be analyzed on an aggregated level (per GP practice). The primary outcome is the percentage of correctly registered diagnoses of type 2 diabetes. The key secondary outcome is the registration of chronic kidney disease. Exploratory secondary outcomes are the registration of heart failure, biometric data and lifestyle habits, and the evolution of 4 different EHR-extractable quality indicators.

**Discussion:**

This cluster randomized controlled trial intends to primarily improve the registration of type 2 diabetes in the EHR of the GP and to secondarily improve the registration of chronic kidney disease. In addition, the registration of heart failure, lifestyle parameters, and biometric data in the EHR of the GP are explored together with 4 EHR-extractable quality indicators. By doing so, this study aims to improve the data completeness of the EHR, paving the way for future quality assessments.

**Trial registration:**

ClinicalTrials.gov NCT04388228. Registered on May 14, 2020.

**Supplementary Information:**

The online version contains supplementary material available at 10.1186/s13063-021-05259-9.

## Background

The electronic health record (EHR) is an important instrument that, when properly implemented, can be used as a tool to improve the quality of healthcare [1]. However, many challenges need to be overcome to use the vast amount of EHR-stored data for quality assessment [2, 3]. One of these challenges is the lack of data completeness of the EHR and, in particular, the varying quality of the correct and complete registration of diagnoses [4–6]. After all, when the quality of care for certain diseases needs to be evaluated, the number of registered diagnoses of these diseases in the problem list of the EHR needs to be as accurate as possible to have reliable results in our quality measurement. In the past, data quality feedback tools and frameworks have been developed to address the problem of the lack of data completeness [7, 8].

Chronic diseases such as diabetes mellitus type 2 (DM 2) and chronic kidney disease (CKD) have a high prevalence, and the quality of primary care for these conditions needs improvement [9, 10]. For example, CKD can be identified in the EHR with the help of the electronic CKD phenotype, which has proven to be an accurate method to detect patients likely to have CKD based on data stored in the EHR [11]. However, there is still the need for effective organizational and technical strategies to achieve data completeness [12]. The electronic CKD phenotype is thus an important first step, but additional pragmatic trials to explore implementation strategies incorporating this electronic CKD phenotype are necessary [13]. An implementation strategy that can be useful for this purpose in primary care could be audit and feedback (A&F).

Audit and feedback is a well-known quality intervention that, according to the last Cochrane review, leads to “small but potentially important improvements in professional practice” [14]. However, the important features of A&F and their influence on the effect of an A&F intervention are still the subject of debate [15]. Previous work identified some testable and theory-informed hypotheses for designing an A&F intervention, and suggestions to improve the interventions’ effectiveness are available in the literature [16, 17]. Some features of the feedback are known to be effective, for example, the frequency of the feedback provision (more than once), but other features, such as the use of benchmarks as a comparison, the evidence-based quality of the feedback, and a low cognitive load of the feedback, need further investigation [14, 16–19]. Therefore, the aim of this study is to investigate whether an automated A&F intervention, using different features of feedback, can be effective in improving the data completeness of the EHR in primary care.

## Methods

### Study design and objectives

#### Study design

The study is a pragmatic cluster randomized controlled trial (CRCT) with a superiority framework and an intervention at the level of the general physician (GP) practice. The protocol is reported according to the Standard Protocol Items: Recommendations for Interventional Trials (SPIRIT) checklist [20] (see additional file 1 and Fig. 1).

**Fig. 1 Fig1:**
[figure not shown]
Time schedule. DM 2, diabetes mellitus type 2; CKD, chronic kidney disease; EHR, electronic health record

#### Primary objective

The primary objective of this study is to improve the quality of registration of DM 2 in GP EHR.

#### Key secondary objective

Improve the registration of CKD

#### Exploratory secondary objectives

Evaluate the registration of heart failure, biometric data, and lifestyle habits (smoking, exercise, weight, height, alcohol use)Two different EHR-extractable quality indicators for DM 2 and two different EHR-extractable quality indicators for CKD will be evaluated to investigate whether an improved registration of these two diseases has an impact on EHR-extractable quality indicators.

### Study population, eligibility criteria, and data storage

This trial has GP practices as the level of allocation. All GPs in the Intego network will be asked to participate in this trial. For GPs working in a group practice, the whole group will be asked to collaborate. GP practices are excluded when participation is not unanimous. Intego is a Belgian general practice-based morbidity registration network at the Center of General Practice of the University of Leuven [21]. Intego collects data on health parameters, incidence and prevalence rates, laboratory results, and prescribed drugs for all relevant subgroups. As of 2020, 395 GPs of 106 practices spread throughout Flanders, Belgium, collaborated in Intego. In order to ensure enough GP practices take part in the trial, all the GP practices will be contacted and/or visited individually and asked to take part in this trial. An Intego researcher will explain the study and request informed consent. The researcher will also emphasize that the provision of the feedback is an incentive on its own. Therefore both groups will receive feedback although the feedback in the control group will be basic. In addition, the Intego researcher will also inform the participants that the intervention will not be intrusive since it will be integrated (automated) in the normal workflow of the GP (to optimize the use of the EHR-system).

The inclusion criteria for GP practices participating in this trial are the same criteria as for inclusion in the Intego network, which are explained in more detail elsewhere [21, 22]. Only the aggregated data of patients 40 years or older who had at least one consultation the past year will be analyzed for both primary and secondary outcomes.

The data will be hosted on the Healthdata.be platform, which is described in more detail elsewhere [22].

### Intervention

The intervention consists of an extended electronically delivered feedback report with multiple components that will be delivered 4 times electronically into GP practices over 12 months. The extended feedback report is generated based on an automated audit that is built into the EHR of the GP. This audit will be executed on the Intego database in an automated fashion 4 times and is available in both the control and intervention groups. The feedback report for both trial arms will be provided on the independent Healtstat.be platform. The intervention group will also receive the extended feedback report through a push system into their e-health inbox to minimize the effort to consult it. The aim of the push system is to involve participating GPs and to actively direct their attention to the task at hand, namely, the registration of diagnosis and parameters in the EHR.

The extended feedback report will be delivered in the form of action plans and goals consisting of multiple components:
Benchmarking of the results of the audit with peers on disease-specific laboratory results or medication prescriptions. The results of the audit will be compared with the mean of the 10% best performers according to the Achievable Benchmarks of Care (ABC) method [23].A low cognitive load of the feedback, such that the results will be presented with the help of graphs and without too many in-depth elements.Guidance on which codes to use for which cases or where to put the information in a structured way.Links to disease-specific guidelines.A push system to minimize the effort the GP must make to consult the feedback.

The aim of the automated audit is to identify the unregistered population, and this built-in audit is available in both study arms. The aim of the extended feedback report is to improve the registration level in the EHR and thus improve the data completeness of the EHR.

The control group will also have access to the automated audit since it is built in the EHR and will receive basic feedback on the level of registration in their EHR. The feedback will only be available on HealtStat.be through a pull system, so GPs will need to actively check Healtstat.be. For a detailed comparison of control versus intervention, please see Table 1.

**Table 1 Tab1:** Intego feedback trial: control versus intervention group

	Control group	Intervention group
Four different feedback moments and reports over 12 months on the following: - The registration level of DM 2 - The registration level of CKD - The registration level of lifestyle habits: the number of patients with lifestyle factors registered in the EHR; lifestyle factors = smoking, alcohol use, exercise, weight, height - The registration level of heart failure	• Diagnostic built-in audit on registration of (parameters of) DM 2, CKD, heart failure and lifestyle habits available in the EHR CareConnect®	
	• Basic feedback available at Healthstat.be • Feedback = percentages per registered diagnosis/parameter per GP practice in text • Pull system where the GP needs to actively check for feedback by logging in on the website of Healthstat.be	• Extended feedback in the form of action plans and goals consisting of the following: o Percentages per registered diagnoses/parameters per GP practice, presented in graphs with low cognitive load o Benchmarking with peers on disease-specific lab results and/or with the percentage of patients who receive disease-specific medication (ABC method) o Guidance on which codes to use for which cases or where to put the information in a structured way o Links to disease-specific guidelines • Available at Healthstat.be • Push system to eHealth inbox to minimize the effort necessary to consult it

*DM 2* diabetes mellitus type 2, *CKD* chronic kidney disease, *EHR* electronic health record, *GP* general physician, *ABC* Achievable Benchmarks of Care method

### Allocation concealment and random sequence generation

The list of participating practices will be known at the start of the trial. The allocation sequence will be performed by a statistician (independent from the research group) and it will be generated using covariate-based constrained randomization [24]. More specifically, out of a list of all acceptable allocations one allocation scheme will be drawn at random. To balance the mean size of the practice between both groups, a list of all possible allocations (restricted to those allocations with equal number of practices in each group) with a maximal difference of 5% in mean number of patients per practice and a maximal difference of 5% in total number of patients will be created and one allocation will be drawn at random from this list [24]. The covariate-based constrained randomization procedure will be implemented using a SAS-macro [25]. If the trial would start before all practices are known, practices with “late entry” will be allocated using minimization [26], categorizing the number of patients per practice into 2 or 3 categories.

The control versus intervention group will be allocated in a 1:1 manner. GPs are not blinded to the intervention. The research facility will be blinded to the allocations until all data are collected.

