### Power calculation

To measure an improvement in our primary and key secondary outcome, these are the percentage of registered DM 2 and CKD diagnoses in the EHR, a power calculation was performed.

To measure an improvement of 10% points (from 75% to 85%) in our primary outcome with 80% power, an alpha of 0.05, a variance inflation factor (VIF) of 21.12 (based on an intra-class correlation (ICC) of 0.103), we need 56 practices to be included in this CRCT, or 28 practices in each group (Table 2). To measure an improvement of 20% points (from 50% to 70%) in our key secondary outcome with 80% power, an alpha of 0.05, a VIF of 9.1, and an ICC of 0.32, we need 68 practices to be included in this CRCT, or 34 practices in each group (Table 2). To have enough statistical power to measure an improvement in both outcomes, 68 practices will be recruited. The VIF and ICC were calculated based on historical data from the Intego database and were used to correct for clustering.

**Table 2 Tab2:** Power calculation

	Assumed % correct diagnoses						Required number		
	C	I	Alpha	N0 (total)	ICC	VIF	Mean per practice	N patients	N practices

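### Baseline registration level of each practice is neither balanced at randomisation nor adjusted for in the analysis, so avoidable chance imbalance and imprecision remain

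*Protocol article*

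**What the plan says.** All references are to the Protocol article.

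- **Allocation concealment and random sequence generation.** The stated aim is "To balance the mean size of the practice between both groups". The plan builds "a list of all possible allocations (restricted to those allocations with equal number of practices in each group"), keeps those "with a maximal difference of 5% in mean number of patients per practice and a maximal difference of 5% in total number of patients", and draws one at random. The same paragraph puts it more loosely: "out of a list of all acceptable allocations one allocation scheme will be drawn at random". On implementation it says only "The covariate-based constrained randomization procedure will be implemented using a SAS-macro [25"]. Practices that enter late "will be allocated using minimization [26], categorizing the number of patients per practice into 2 or 3 categories". No other covariate is named.
- **Analysis.** The effect is estimated with a logistic GEE model and reported as a difference in proportions. The section states that the model will contain no covariates.
- **Power calculation and Table 2.** The ICCs are 0.103 (DM 2) and 0.32 (CKD), and the VIFs are 21.12 and 9.1. "The VIF and ICC were calculated based on historical data from the Intego database". The recruitment target is 68 practices.
- **Data collection.** Data from these practices are extracted weekly as part of the basic Intego project.

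**The concern.** Constrained randomisation exists to stop a trial with few clusters from drawing an allocation that is unbalanced on what predicts the outcome. Here the outcome is a practice's registration level at follow-up, and the natural predictor is the same practice's registration level at the start. The protocol's own ICCs show that practices differ widely on it, most of all for CKD. The plan uses the constraint for size only and then closes the other route, adjustment in the model.

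At stake are the precision and credibility of the one allocation that is realised. If the arms start several points apart, readers will ask how much of the reported difference was there before the first feedback report, and the planned model cannot answer.

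Two smaller faults sit in the same paragraph. The second size limit adds nothing to the first, and the list it describes is too long to create.

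**Working it through.** **1. Reproduce the plan's figures.** Two-proportion formula, two-sided alpha 0.05, 80% power, no continuity correction:
- DM 2: N0 = 2 x 250 = 500; 500 x 21.12 = 10,560; 10,560 / 192 = 55.0, rounded up to 56 practices.
- CKD: N0 = 2 x 93 = 186; 186 x 9.1 = 1692.6; 1692.6 / 25 = 67.7, rounded up to 68 practices.

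Both match Table 2, so the ICCs and VIFs can be used as the authors used them.

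**2. Spread between practices.** SD = sqrt(ICC x p x (1 - p)), taking the control rates as baseline rates (an assumption):
- DM 2: sqrt(0.103 x 0.75 x 0.25) = 0.139, or 13.9 points.
- CKD: sqrt(0.32 x 0.50 x 0.50) = 0.283, or 28.3 points.

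**3. Chance gap between arms at baseline.** With K = 68 practices and mean denominator m, SE = sqrt(p(1 - p) x VIF x 4 / (K x m)):
- DM 2: sqrt(0.1875 x 21.12 x 4 / (68 x 192)) = 0.0348. The 95% range is about +/-6.8 points. P(gap >= 5 points) = 0.151.
- CKD: sqrt(0.25 x 9.1 x 4 / (68 x 25)) = 0.0732. The 95% range is about +/-14.3 points. P(gap >= 10 points) = 0.172.

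Counting between-practice variation alone (SE = SD x sqrt(4/K)) gives 3.4 and 6.9 points, and probabilities of 14% and 15%. The thresholds are half of the 10-point and 20-point target effects.

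**4. How much of a gap reaches the estimate.** This depends on the practice-level correlation r between baseline and follow-up, which the documents do not give. With similar spread at both times, the expected carry-over is r x gap:

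| Assumed r | 5-point DM 2 gap | 10-point CKD gap |
|---|---|---|
| 0.5 | 2.5 points | 5 points |
| 0.7 | 3.5 points | 7 points |

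**5. Precision forgone.** Multiplying the VIF by (1 - r^2), an optimistic approximation to adjusting for baseline, gives this power with 68 practices:

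| | As planned | r = 0.5 | r = 0.7 |
|---|---|---|---|
| DM 2 | 88% | 95% | 99% |
| CKD | 80% | 90% | 98% |

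**6. Would tighter constraints leave room?** Taken singly, P(gap < 2 points) for DM 2 is 0.434 and P(gap < 4 points) for CKD is 0.415. About 52% to 19% of allocations meet the 5% size limit if the coefficient of variation of practice size is 0.3 to 1.0 (assumed). Treating the three criteria as independent, between 0.52 x 0.434 x 0.415 = 9% and 0.19 x 0.434 x 0.415 = 3% meet all of them. Three per cent of 2.8 x 10^19 is still about 10^18 allocations.

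**7. Constraining without adjusting.** If the DM 2 gap is held within 2 points (2 / 3.48 = 0.57 SE) but the model stays unadjusted, the nominal 5% test has a true type I error of about 2.6% at r = 0.5 and 0.9% at r = 0.7 (simulation). The intervals are then too wide.

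**8. The two wording points.** With k practices in each arm, (T1/k - T0/k) / (T0/k) = (T1 - T0) / T0, so the limits on mean and total are the same limit. The number of equal-arm allocations is C(68,34) = 2.8 x 10^19, which at 10^9 per second would take about 900 years to list.

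**The case against.** The strongest reply is that nothing here is invalid. Balancing on cluster size is a legitimate choice, randomisation is unbiased in expectation, and the 15% and 17% are tails of the very sampling variation that the VIFs already build into the sample size. All of that stands. A reader might infer that the trial is biased, underpowered or has an inflated type I error. The documents support none of these: 68 practices give the stated 80% power, and the GEE interval covers this variation.

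A reader might also infer that a baseline gap passes in full into the effect estimate. That would need a correlation near 1. Persistence is plausible, since a registered diagnosis normally stays on record, but both arms receive the audit and some feedback, which may reorder practices.

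It is also fair to say that availability of baseline values at allocation is an inference from the weekly extraction and the historical ICCs, not a statement in the text. The inference is a strong one.

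On the list of allocations, the cited macro may well sample instead of enumerating, and an article need not give such detail. It would be wrong to conclude that the randomisation cannot be carried out; only the literal wording fails. The duplicate limit excludes no allocation and does no harm.

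The reply does not remove the main point. The absence of adjustment is not a detail left to an unseen analysis plan, because the article states it outright.

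**Conclusion.** The point holds as a worthwhile, inexpensive improvement to the design and analysis, not as an error that invalidates them. Baseline registration level is controlled neither at allocation nor in the model. With 68 practices, the chance of a baseline gap of at least half the target effect is about 15% for DM 2 and 17% for CKD. CKD has most to gain, because 68 practices is exactly its requirement for 80% power.

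These figures assume that the historical ICCs and VIFs apply, that baseline rates are near 75% and 50%, and that registration level is unrelated to practice size. How far a gap affects the estimate, and how much precision adjustment would recover, depends on a correlation that the documents do not give; the values of r above are illustrations. The redundant limit and the unlistable allocations are corrections of wording only.

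**What to change.** 1. **Randomisation.** Add maximal differences in mean baseline DM 2 and CKD registration to the constraint, for example 2 and 4 points. Use baseline registration category as a further minimisation factor for late entrants.
2. **Analysis.** Replace the statement that no covariates are used. Adjust the GEE model for each practice's baseline registration level of the outcome concerned and for practice size, and obtain the difference in proportions by standardising over these covariates. This has to accompany step 1; constraining alone would make the intervals too wide.
3. **Wording.** Drop the limit on total patients. State that the scheme is drawn from a large random sample of acceptable allocations (for example 100,000 distinct ones) and not from a list of all of them.

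**Cost.** Extra input columns for the macro, an allocation space that is smaller but still of the order of 10^18, and a slightly more complex model. On the dates under Trial status, recruitment had yet to begin when this version was written, so the change could be made before any practice is allocated.

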### Outcomes

Our primary outcome is the registration level of DM 2. This registration level will be expressed as the percentage of registered diagnoses of DM 2 in the EHR. The numerator will be the number of registered diagnoses of DM 2 in the EHR, and the denominator will be the number of patients with a prescription of diabetes medication (ATC classification A10) or with elevated levels of HbA1c (at least once > 53 mmol/mol) or with abnormal fasting glycemia (2 independent measurements > 126 mg/dl). For the primary outcome, we hypothesize that the intervention can achieve an improvement of 10% points (from 75% to 85%) in registration level within 12 months.

As a key secondary outcome, we will focus on the registration of CKD. The registration of CKD will be expressed as the percentage of registered CKD diagnoses in the EHR, with the numerator the number of registered diagnoses of CKD and the denominator the number of patients with a decreased (≤ 45 mL/min/1.73 m^2^) estimated glomerular filtration rate (eGFR). For the registration of CKD, we hypothesize the intervention can achieve an improvement of 20% points (from 50% to 70%) in registration level because preliminary analyses show the quality of registration of CKD is lower than for the primary outcome.

As exploratory secondary outcomes, we will evaluate the registration of heart failure, lifestyle factors (such as smoking and alcohol use), and biometric data (such as weight and length), and explore two EHR-extractable quality indicators for CKD and two for DM 2. The registration of heart failure will be expressed as the percentage of heart failure patients, with the numerator the number of registered heart failure diagnoses and the denominator the total active patient population older than 40. Lifestyle factors and biometric data will be expressed as the percentage of patients who have registered lifestyle factors or biometric data in their EHR.

The EHR-extractable quality indicators we will explore are as follows [27, 28]:
Percentage of patients with CKD, in whom the GFR, albuminuria, and total protein is determined at least once a yearPercentage of patients with CKD who are vaccinated with a pneumococcal vaccinePercentage of patients with DM 2 and an eGFR of < 30 mL/min/1.73 m^2^ who no longer receive metformin.Percentage of patients with DM 2 whose HbA1c level is measured at least once every 6 months

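### The DM 2 denominator admits any type of diabetes but the numerator counts only DM 2 codes, so a correctly coded type 1 patient scores as unregistered

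*Protocol article*

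**What the plan says.** The abstract (Methods) describes the endpoint this way: "The primary outcome is the percentage of correctly registered diagnoses of type 2 diabetes". The Analysis section likewise speaks of estimating the proportion correctly registered in each arm.

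The Outcomes section gives the operational rule. Patients enter the denominator "with a prescription of diabetes medication (ATC classification A10) or with elevated levels of HbA1c", or through fasting glucose. In full:

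- Numerator: "The numerator will be the number of registered diagnoses of DM 2 in the EHR".
- Denominator, medication route: "the denominator will be the number of patients with a prescription of diabetes medication (ATC classification A10"). The whole class is named, with no restriction by drug or by type of diabetes.
- Denominator, laboratory routes: "or with elevated levels of HbA1c (at least once > 53 mmol/mol) or with abnormal fasting glycemia (2 independent measurements > 126 mg/dl").

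The only other patient-level filter is in the section on study population: "Only the aggregated data of patients 40 years or older who had at least one consultation the past year will be analyzed". No section removes patients who carry a code for type 1, secondary or another form of diabetes.

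Two features of the Intervention section bear on the point. The audit's purpose is stated as "The aim of the automated audit is to identify the unregistered population" (the sentence goes on to say that it is available in both arms). The extended feedback, in the intervention arm only, includes "Guidance on which codes to use for which cases or where to put the information in a structured way".

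**The concern.** The numerator and the denominator describe different populations. The denominator finds people who probably have diabetes of some type; the numerator asks whether they have a DM 2 code. For patients with another type, the score runs against correct coding:

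- a correct type 1 code adds one to the denominator and nothing to the numerator;
- a wrong DM 2 code adds one to both;
- changing a wrong DM 2 code to the right type lowers the practice's score.

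The trial's purpose is better data in the record, and its primary outcome is described as correct registration. For this subgroup the outcome gives no credit for a correct entry and full credit for an incorrect one. If the built-in audit uses the outcome definition, which the article does not say, it would also list these correctly coded patients as needing registration.

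**Working it through.** **1. The plan's own sample size (Power calculation, Table 2).** Inputs: 75% and 85%, two-sided alpha 0.05, power 80%, VIF 21.12, mean denominator 192 per practice.

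Per arm, with pooled variance and no continuity correction:

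n = [1.96 × √(2 × 0.80 × 0.20) + 0.84 × √(0.75 × 0.25 + 0.85 × 0.15)]² / 0.10² = 250, so N0 = 500.

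500 × 21.12 = 10,560 and 10,560 / 192 = 55.0, rounded up to an even 56. All three stated figures reproduce, so the power arithmetic is not at fault.

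**2. Effect of the definition on the level.** Let s be the share of the denominator with another type of diabetes, all correctly coded, and let π be the registration level among true type 2 patients. With the numerator restricted to denominator patients (the article does not state this restriction):

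observed level = π × (1 − s), with maximum 1 − s.

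The article does not give s. The range 3% to 8% is an assumption.

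| s | Maximum level, 1 − s | Such patients in a practice of 192 | True type 2 levels if 75% and 85% are on the published denominator |
|---|---|---|---|
| 3% | 97% | 5.8 | 0.75/0.97 = 77.3% to 0.85/0.97 = 87.6% |
| 5% | 95% | 9.6 | 78.9% to 89.5% |
| 8% | 92% | 15.4 | 81.5% to 92.4% |

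For example, a practice with s = 8% that has coded 85% of its true type 2 patients scores 0.85 × 0.92 = 78.2%.

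**3. Does the planned difference shrink?** That depends on what the 75% and 85% refer to. The Outcomes section states them for the registration level, a term it has just defined with this numerator and denominator. Read that way, the 10 points are already on the mixed denominator and nothing shrinks.

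Only if 75% and 85% were true type 2 levels would dilution apply. At s = 8% the observed levels would be 69.0% and 78.2%, a difference of 9.2 points. With 68 practices the effective number per arm is 68 × 192 / 2 / 21.12 = 309, and power would be about 0.74, against 0.88 at s = 0. At s = 5% it would be 0.79. The document does not support that reading over the first.

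**4. Does it inflate the ICC?** The between-practice variance implied by the plan is 0.103 × 0.75 × 0.25 = 0.0193. If s varied uniformly from 3% to 8% across practices, its SD would be 0.05/√12 = 0.0144. With π taken as 0.80, it would contribute (0.80 × 0.0144)² = 0.00013, which is under 1% of 0.0193. The Power calculation section also says that the ICC came from historical Intego data. If the same definition was used there, this variation is already inside 0.103.

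**The case against.** The strongest reply is that the definition is the same in both arms, practices are randomised 1:1, and the reported effect is a difference in proportions. Patients with other types of diabetes should lower both arms' levels alike. The 85% target lies below even the 92% ceiling. A denominator built from prescriptions and laboratory values is a reasonable pragmatic choice when diagnosis codes are the very thing under doubt. All of this stands, and it limits the point to what the measure means.

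A reader might infer three stronger things, and the document supports none of them.

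- *The trial loses power or the ICC is inflated.* Steps 3 and 4 of the working show that the first depends on a reading the text does not favour, and that the second is negligible or already counted.
- *The intervention will drive miscoding.* If every such patient in one arm were recoded as DM 2, the level would rise by s, that is 3 to 8 points under the assumed range. Nothing suggests that this would happen. The article describes no payment or sanction tied to the score, both arms see their registration percentages, the peer benchmark is described for laboratory results and medication, and the coding guidance works against it.
- *The intervention could look worse by improving coding.* That would need corrections away from DM 2 to outnumber newly coded type 2 patients. The article gives no basis for this.

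It may also be said that *correctly* is loose wording and that the aim is completeness. But the word appears in the abstract's statement of the primary outcome and again in the Analysis section. Nor is this a detail left to another document: the Outcomes section gives a full rule, with thresholds, and the rule itself misclassifies these patients.

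**Conclusion.** The point holds as a mismatch between the stated outcome and its definition. Patients correctly coded with type 1 or another diabetes type count as unregistered, and a DM 2 code for them would count as success. This follows from the definition alone.

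Its size is unknown, because s is not in the document. Under the assumed 3% to 8% the ceiling is 97% to 92%, or roughly 6 to 15 patients in a practice of average size. The age limit of 40 does not remove these patients. Past gestational diabetes is a weak example, because whether such patients qualify depends on a look-back period that the article does not state.

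No bias between arms, loss of power or inflation of the ICC is shown. The point concerns the validity of the primary outcome and should be settled before the first feedback round.

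**What to change.** Exclude from the denominator patients who have a registered non-type-2 diabetes code at the baseline snapshot, and count in the numerator only patients who are in that denominator. Apply the rule identically in both arms. Fixing it at baseline keeps recoding after randomisation from changing who is analysed. Narrowing the A10 route alone would not be enough, because the laboratory routes admit the same patients.

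Add two sensitivity analyses:

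1. the denominator as published, without the exclusion;
2. any registered diabetes-type code counted as registered. This also deals with patients who have no code at baseline and are then correctly coded as another type, and with wrong DM 2 codes that are corrected during the trial.

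Recompute the 75% and the ICC of 0.103 on the revised denominator from the historical Intego data, and confirm that 56 practices, and hence the planned 68, still suffice.

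The cost is one exclusion in the extraction query, using codes already in the record, plus the recalculation. The downside is that true type 2 patients miscoded as another type at baseline drop out of the main analysis; the first sensitivity analysis keeps them.
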